**Participants**

Eligible participants are employees at each of the six workplaces, providing informed consent. As employees of these companies, participants will be adults with the ability to read English. Employees will need to gain access to the Internet to participate in this study.

**Recruitment**

Occupational health leads will be consulted on the most suitable recruitment procedure for their organisation. Recruitment methods include: email, article on company web-portal or newsletter, or via posters. Occupational health leads will be asked to provide the reasons why they chose their preferred methods. Employees will be invited to complete an online health screen and to take part in a study led by researchers from UCL and NCL. If interested in learning more about the study, employees are invited to visit the study website, via hyperlink within emails, on web-portals or electronic newsletters. The study website will present the employee with participant information pages, which will explain the aim of the study, what will be involved if taking part, the potential advantages and disadvantages of participation and the implications of the findings. It will be made clear that taking part is voluntary, that their employer will not know whether they have taken part, and that all the information they provide will be anonymised (i.e. not linked with their name). If happy to take part, employees will be asked to complete an online consent form. On completion of the consent form, participants will be asked to complete the health screen (as detailed below).

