The World Health Organisation recommends the provision of personal health resources, as one of the four ways of achieving a healthy workplace, which may include healthy food choices, campaigns to encourage physical activity, no smoking policies and health assessments ([24](#_ENREF_24)). There is some evidence on the effectiveness of health resources delivered in the workplace but this largely concentrates on physical activity (for which there is NICE guidance specifically for this setting ([25](#_ENREF_25))), diet and smoking ([24](#_ENREF_24)). The challenges facing SBI for alcohol misuse in the workplace setting may explain the lack of research in this field. Alcohol consumption is a sensitive topic. The perceived repercussions of divulging sensitive information in-person may affect self-reported veracity ([26](#_ENREF_26)). It is possible that employees will under report their alcohol intake in the workplace setting, where there may be concerns over the confidentiality of their responses. There is a limited literature on how employees feel about answering questions on their health in the workplace. There may be concerns that the information they provide may impact on their employment thus deterring employees from participating in such activities, or leading them to report less than they are actually drinking. Using the Internet to confidentially deliver screening and brief intervention may tackle some of the concerns employees may have with SBI in this setting.

*Online interventions for reducing alcohol intake*

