**Baseline data collection**

*Health screen*

Participants will be asked to answer questions of a range of behaviours known to impact on their health and wellbeing, namely alcohol, smoking, diet and physical activity. The 3-item AUDIT-C questionnaire will be used as an initial screen for alcohol misuse ([37](#_ENREF_37)), with a score of five or more indicating consumption above recommended limits ([36](#_ENREF_36)). The AUDIT-C comprises the first 3 consumption questions from the WHO Alcohol Use Disorders Identification Test (AUDIT) ([38](#_ENREF_38)). Questions relate to the frequency of alcohol consumption, quantity of alcohol consumed on a typical drinking day, and frequency of drinking more than 6 (women) or 8 (men) drinks on one occasion. For participants scoring 5 or more on the AUDIT-C, the remaining seven questions of the AUDIT will then be presented which focus on alcohol-related harm. Questions on smoking status, consumption of fruit and vegetables and level of physical activity will also be included in the health screen, using the same approach as the HOW study ([36](#_ENREF_36)).

*Demographics*

Participants will be asked to provide demographic information, consisting of gender, year of birth, ethnicity, occupational classification (categories to be supplied by the occupational health lead from each organisation). Participants will also be asked to provide an email address that will allow them to be contacted again in three months’ time. Demographic data will be collected at the end of the health screen, before provision of feedback on health behaviours.

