**Follow-up data collection**

All participants will be contacted by email three months after baseline data collection to complete follow-up questionnaires online. The emails will contain a hyperlink to the online battery of questionnaires. All participants will receive the same questions at follow-up. Details of the type of data collected at follow-up are provided below under *Outcomes and outcome measures*.

The study will be registered with the UCL data protection officer. The data will be collected and stored in accordance with the Data Protection Act 1998 and will be disposed of in a secure manner. Participants will automatically be assigned a unique identifying number when consenting to take part in the study. All outcome data will be anonymised and identifiable only by the unique ID number. Data will be automatically loaded into a secure, password protected, on-line database, which can only be accessed by the research team. The following measures will be taken to ensure data security:

•The webserver will be protected by a firewall

•Personal data will be encrypted and entered via data entry pages hosted on a Secure Server (https://)

•Email addresses, personal data and research data will be stored in separate, distinct database tables

•Access to database tables will be strictly limited to those actively involved in the project, who will be issued with a username and password

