**Outcomes and outcome measures**

The outcomes will reflect the objectives of this feasibility study, which include 1) estimation of study parameters to inform the sample size calculation for a definitive multicentre trial; 2) acceptability and potential risk to employees of participation; 3) engagement with an extensive online alcohol intervention and its suitability for this population.

Outcome measures will include the AUDIT and a questionnaire designed by the research team that explores the acceptability and potential risk of delivering electronic screening and brief intervention to employees in the workplace. The questionnaire will also include questions on whether participants engaged with the online alcohol intervention (detailed below).

*Estimating study parameters*

For organisations that choose to recruit participants via email, rates of eligibility will be determined by the number of employees with a work email address as a percentage of the total workforce at each organisation. These data will be provided by the occupational health leads for each organisation. Occupational health leads will also provide information on the different types of jobs / occupational classifications within the organisation, and which of these require a work email address. This information will highlight any inequalities introduced by restricting inclusion to those employees with a work email address. The number of employees who complete the health screen (and therefore consent to participate in the study) will be reported as a percentage of the total number of employees invited to participate in the study via email, for each organisation. The number of participants scoring five or more on the AUDIT-C will be reported as a percentage of those who have completed the health screen. Finally, the number of participants who complete follow-up questionnaires at three months will be reported as a percentage of those participants completing the health screen, for each organisation.

*Acceptability and potential risk*

The follow-up questionnaire will ask participants about the acceptability of answering questions on their health and receiving feedback online in a workplace setting. There are questions on use of technology, sensitivity of questions, time taken to participate at work and the confidentiality of responses. Participants will be asked if they have any concerns with this approach, including the possible harm to the employee.

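### What employees are told overstates the plan: the data are coded rather than anonymised, and the promise that the employer will not know is not secured if a work email address is given

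*Protocol*

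**What the plan says.** The protocol's Recruitment section describes what the study website will make clear to employees before consent: that "their employer will not know whether they have taken part, and that all the information they provide will be anonymised". It adds a gloss on the last word, "i.e. not linked with their name".

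Under Demographics, the Baseline data collection section lists what is asked at the end of the health screen: "gender, year of birth, ethnicity, occupational classification (categories to be supplied by the occupational health lead from each organisation"). It continues: "Participants will also be asked to provide an email address that will allow them to be contacted again". The type of address, work or personal, is left open.

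The Follow-up data collection section gives each participant a unique identifying number at consent and says of the resulting data: "All outcome data will be anonymised and identifiable only by the unique ID number". Among its security measures is that "Email addresses, personal data and research data will be stored in separate, distinct database tables". It also lists a firewall, encrypted entry over a secure server, and access restricted to the research team. All participants are emailed a link to the questionnaires three months after baseline.

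The Background explains why this matters in a workplace: "There may be concerns that the information they provide may impact on their employment". The acceptability questionnaire, under Outcomes and outcome measures, asks among other things about "time taken to participate at work and the confidentiality of responses".

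**The concern.** Employees are given two unqualified assurances before they report their drinking: the information is anonymised, and the employer will not learn that they took part. The first does not match the data handling set out later in the same protocol. The second depends on something the protocol does not control, namely which email account the participant uses.

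The Background treats fear of consequences at work as a possible cause of non-participation and under-reporting, and offers confidential online delivery as a way to ease it. How confidentiality is described is therefore central to the design. Consent should rest on an accurate account of it, and a plausible route by which an employer could learn of participation should be closed or disclosed.

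**Working it through.** No figure in the protocol bears on this point and no arithmetic applies. The check is to set each assurance beside the procedure that has to deliver it.

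**Assurance 1: all the information is anonymised.**

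1. The email address is something participants provide, so it falls within the assurance. It is a direct means of contacting an individual and may show a name; the protocol does not exclude addresses that do.
2. A unique ID is assigned at consent, and the outcome data are said to be both anonymised and identifiable through that ID. Data that can be traced through a key held by the study are coded. The sentence "All outcome data will be anonymised and identifiable only by the unique ID number" uses two terms that do not fit together.
3. The design relies on the link. Each participant is emailed three months after baseline, so addresses must be usable against study records. The section on engagement with Down Your Drink compares baseline characteristics of participants who register with those who do not, which calls for person-level matching to the baseline record.
4. Keeping addresses, personal data and research data in separate tables lowers the risk of disclosure. It does not remove the link.

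Result: the description that fits the procedures is confidential and coded, with the address held apart.

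**Assurance 2: the employer will not know who took part.**

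1. Invitations go out by email, web-portal, newsletter or poster. They reach staff whether or not they take part, so receiving one reveals nothing.
2. The three-month email is different: it goes to participants. Its arrival in a mailbox is itself a sign of participation.
3. The email field accepts any address. Recruitment through work email is one of the planned methods, so some participants may well give that address.
4. The firewall, encryption, secure server, separate tables and access limits all act on the study's systems. None reaches the participant's mailbox.

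Result: the promise holds for a participant who gives a non-work address, as far as this route is concerned. It is not secured for one who gives a work address. The share giving a work address is not stated, so the range is 0 to 100%. An unconditional promise needs a control that makes that share irrelevant, and the protocol has none.

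**The case against.** The strongest reply is that the protocol defines its term. Anonymised is glossed as "i.e. not linked with their name", and no name is requested. On that reading the promise fails only where an address shows a name. This has force: it narrows the promise, and it means one cannot say the statement is false for every participant. It does not make the wording accurate, because the assurance covers all the information provided, including an address that identifies many people as well as a name would.

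A second reply is that the protection is real. This stands. A reader might infer that the safeguard against the employer does not exist, or that the assurance is the only protection offered. The Follow-up data collection section contradicts both: it registers the study with the data protection officer, separates the tables, encrypts personal data and limits access to the research team.

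A third reply is that nothing goes to the employer. This also stands. A reader might infer that inviting staff through employer channels reveals who took part. It does not: those channels are described for the invitation, consent and screening take place on the study website, and no part of the protocol gives occupational health leads individual participation or response data. What remains is narrower: a participant gives a work address, and the employer can see that mailbox. The protocol states neither. The point is that the promise is made without any condition that would exclude them.

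Finally, the information pages themselves are not available here and may explain the coding. The Recruitment section nevertheless fixes what they are to make clear, and that commitment is what needs changing.

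**Conclusion.** The point holds as a mismatch between what participants are to be told and what the study does. The anonymity statement describes coded data, which follows from the protocol's own text. The employer promise is not secured for anyone who gives a work address. That second part rests on two assumptions: that some participants give one, and that the employer is able to see the account.

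The size cannot be put as a number. The protocol gives no figure for the share using work addresses, and a count of participants would not show that anyone is exposed. No estimate, sample size or planned analysis is affected. A reader might also infer that the acceptability results on confidentiality would be invalid. The documents do not support that: the questionnaire asks directly about confidentiality and concerns, and nothing shows that a definitive trial could not work under the corrected wording.

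The change is still worth making before the information pages go live, because it makes consent accurate at almost no cost.

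**What to change.** - **Recruitment section and information pages:** replace the anonymity statement with *confidential and coded, with your email address held separately and linkable only by the research team*. Replace the employer promise with *the study team will not tell your employer*.
- **Baseline data collection, email field:** invite a non-work address where the participant has one, and note that work accounts may be visible to the employer.
- **Follow-up data collection:** reword the sentence on the unique ID so that it calls the data coded, in line with the new participant wording. Keep the listed security measures as they are.

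The cost is a few lines of text on the information pages and one line at the email field. The more candid statement may put off a few employees. Some may have only a work address; they can still take part, having been told what that means.

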**Baseline data collection**

*Health screen*

Participants will be asked to answer questions of a range of behaviours known to impact on their health and wellbeing, namely alcohol, smoking, diet and physical activity. The 3-item AUDIT-C questionnaire will be used as an initial screen for alcohol misuse ([37](#_ENREF_37)), with a score of five or more indicating consumption above recommended limits ([36](#_ENREF_36)). The AUDIT-C comprises the first 3 consumption questions from the WHO Alcohol Use Disorders Identification Test (AUDIT) ([38](#_ENREF_38)). Questions relate to the frequency of alcohol consumption, quantity of alcohol consumed on a typical drinking day, and frequency of drinking more than 6 (women) or 8 (men) drinks on one occasion. For participants scoring 5 or more on the AUDIT-C, the remaining seven questions of the AUDIT will then be presented which focus on alcohol-related harm. Questions on smoking status, consumption of fruit and vegetables and level of physical activity will also be included in the health screen, using the same approach as the HOW study ([36](#_ENREF_36)).

*Demographics*

Participants will be asked to provide demographic information, consisting of gender, year of birth, ethnicity, occupational classification (categories to be supplied by the occupational health lead from each organisation). Participants will also be asked to provide an email address that will allow them to be contacted again in three months’ time. Demographic data will be collected at the end of the health screen, before provision of feedback on health behaviours.

**Intervention**

All participants will receive instantaneous feedback from the health screen in-line with standard NHS recommendations for healthy living. Participants who drink within recommended limits, do not smoke, eat five or more portions of fruit and vegetables a day or undertake 150 minutes or more of moderate or vigorous physical activity a week will be congratulated for leading a healthy lifestyle and reducing their risk of heart disease or cancer, for example. Participants who drink above recommended limits, smoke, eat less than 5 portions of fruit and vegetables a day or do less than 150 minutes of moderate or vigorous physical activity a week will receive feedback on the governments recommendations and the benefits of changing their behaviour (to reduce their risk of harm). This brief advice will be accompanied by hyperlinks to corresponding pages of the NHS Choices and NHS Livewell websites for further information. Participants drinking above recommended limits will receive brief advice on the harms of excess drinking, along with a hyperlink to the Down Your Drink website. The Down Your Drink website is for people wanting to determine how much they are drinking, whether it is a problem for them and for support with making changes. Down Your Drink is an extensive online brief intervention and may or may not be used or needed by all employees. This will be explored in the follow-up questions.

*The Down Your Drink website*

Down Your Drink is aimed to help adults from the general population to reduce their drinking. It was developed and evaluated by a team based at UCL, with funding from the AERC and NPRI. DYD is based on approaches known to be effective at motivating, eliciting and maintaining change, including motivational enhancement, cognitive behavioural therapy, and relapse prevention. The programme helps people reach high-quality decisions about whether to change their drinking; helps plan a specific change and provides the tools needed to cut down; provides support with maintaining change and avoiding relapse. DYD also contains a number of ‘e-tools’, central to which is the ‘Drinking Episode Diary’. The diary allows users to record their alcohol consumption and their thoughts and feelings surrounding each drinking episode. The Drinking Episode Diary also calculates the cost and calories related to consumption each day. Other interactive features include a blood alcohol level calculator, unit counter, ‘thinking drinking record’ of answers to exercises, and email Tips from the DYD Team on cutting down.

**Follow-up data collection**

All participants will be contacted by email three months after baseline data collection to complete follow-up questionnaires online. The emails will contain a hyperlink to the online battery of questionnaires. All participants will receive the same questions at follow-up. Details of the type of data collected at follow-up are provided below under *Outcomes and outcome measures*.

The study will be registered with the UCL data protection officer. The data will be collected and stored in accordance with the Data Protection Act 1998 and will be disposed of in a secure manner. Participants will automatically be assigned a unique identifying number when consenting to take part in the study. All outcome data will be anonymised and identifiable only by the unique ID number. Data will be automatically loaded into a secure, password protected, on-line database, which can only be accessed by the research team. The following measures will be taken to ensure data security:

•The webserver will be protected by a firewall

•Personal data will be encrypted and entered via data entry pages hosted on a Secure Server (https://)

•Email addresses, personal data and research data will be stored in separate, distinct database tables

•Access to database tables will be strictly limited to those actively involved in the project, who will be issued with a username and password

**Outcomes and outcome measures**

The outcomes will reflect the objectives of this feasibility study, which include 1) estimation of study parameters to inform the sample size calculation for a definitive multicentre trial; 2) acceptability and potential risk to employees of participation; 3) engagement with an extensive online alcohol intervention and its suitability for this population.

Outcome measures will include the AUDIT and a questionnaire designed by the research team that explores the acceptability and potential risk of delivering electronic screening and brief intervention to employees in the workplace. The questionnaire will also include questions on whether participants engaged with the online alcohol intervention (detailed below).

*Estimating study parameters*

For organisations that choose to recruit participants via email, rates of eligibility will be determined by the number of employees with a work email address as a percentage of the total workforce at each organisation. These data will be provided by the occupational health leads for each organisation. Occupational health leads will also provide information on the different types of jobs / occupational classifications within the organisation, and which of these require a work email address. This information will highlight any inequalities introduced by restricting inclusion to those employees with a work email address. The number of employees who complete the health screen (and therefore consent to participate in the study) will be reported as a percentage of the total number of employees invited to participate in the study via email, for each organisation. The number of participants scoring five or more on the AUDIT-C will be reported as a percentage of those who have completed the health screen. Finally, the number of participants who complete follow-up questionnaires at three months will be reported as a percentage of those participants completing the health screen, for each organisation.

*Acceptability and potential risk*

The follow-up questionnaire will ask participants about the acceptability of answering questions on their health and receiving feedback online in a workplace setting. There are questions on use of technology, sensitivity of questions, time taken to participate at work and the confidentiality of responses. Participants will be asked if they have any concerns with this approach, including the possible harm to the employee.

*Engagement with online alcohol intervention (Down Your Drink)*

The number of employees from each organisation who access Down Your Drink, i.e. who register with the website, will be reported. The characteristics (i.e. demographics – collected at baseline) of those participants who register with Down Your Drink will be compared descriptively with those participants who did not register. Of those participants that do register with Down Your Drink, the number of logins and number of pages visited per login will be reported; these data will be collected by Google Analytics.

The follow-up questionnaire will include questions about the Down Your Drink website. Firstly, participants will be asked if they accessed the Down Your Drink website. If they did access Down Your Drink, they will be asked what they like about the website, what they dislike and how it could be improved. There will be a list of tick box options to choose from and a free text box for their own comments. Participants who did not access the website will be asked to provide their reasons. Once again they will be presented with a list of tick box options and a free text box for comments. Participants will also be asked if they have accessed any other alcohol-related resources during the three month study period, and if so, to detail what these resources were.

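### The recruitment rate divides completers from every route by email invitees only, so it is too high where a site mixes routes and has no denominator where a site sends no email

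*Protocol*

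**What the plan says.** **Recruitment rate.** In the Protocol, Outcomes and outcome measures (Estimating study parameters), the numerator is the number of employees who complete the health screen. Nothing limits it to those who came through an email. That number "will be reported as a percentage of the total number of employees invited to participate in the study via email, for each organisation".

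**Eligibility rate.** The same paragraph opens: "For organisations that choose to recruit participants via email, rates of eligibility will be determined by the number of employees with a work email address", taken "as a percentage of the total workforce at each organisation". So work-email holders are the numerator, total workforce is the denominator, and the definition covers email-recruiting organisations only. The paragraph goes on to describe inclusion as limited to staff who have a work email address.

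**Routes.** The Recruitment section leaves the choice to each site: "Occupational health leads will be consulted on the most suitable recruitment procedure for their organisation". It then states: "Recruitment methods include: email, article on company web-portal or newsletter, or via posters".

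**Who may join.** The Participants section says: "Eligible participants are employees at each of the six workplaces, providing informed consent". It adds a need for Internet access and sets no work-email condition.

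**Use of the rates.** Objective 2 names eligibility, recruitment and retention as the study parameters. The Analysis section uses them to help judge whether a definitive trial is feasible, with success criteria left to the statistical analysis plan.

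**The concern.** The Recruitment and Participants sections allow people to enter who were never emailed, while the rate definition counts only emailed people in the denominator. The two fit together only at a site that recruits by email alone.

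Two of the three Objective 2 parameters are touched. The Setting section justifies six diverse organisations partly so that differences in recruitment mechanism and in the number of eligible staff can be explored. With these definitions a non-email mechanism yields no rate, and a mixed-route rate moves with the channel mix as well as with employees' willingness to take part. Differences between sites could then be read as differences in acceptability when they reflect how the study was advertised.

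The fault would also be hard to repair later. Neither the health screen nor the demographic items under Baseline data collection include the route of entry, and no other section provides for logging it.

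**Working it through.** The protocol states no recruitment or eligibility figure, so there is nothing to reproduce. The check compares the definitions and then sizes the mismatch. The protocol gives neither the share of staff emailed nor the share of completers by route, so both are assumed over a range.

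**Inputs from the protocol.** Workforces (Setting): 2,700; 2,900; 19,000; 5,218; 3,500; 700. Target (Analysis): at least 30 participants per site.

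**Step 1: the definitions by type of site.**

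| Site recruits by | Recruitment rate | Eligibility rate |
| --- | --- | --- |
| Email only | Coherent | Defined |
| Email plus other routes | Numerator covers all routes, denominator email only | Defined, but ignores staff without work email who may join |
| Other routes only | Denominator is 0 | Not defined |

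**Step 2: size at a mixed-route site.** Let M be the number emailed, C all completers, and f the share of C who arrived by a non-email route.

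- Rate as written: C/M
- Route-matched email rate: C(1-f)/M
- Ratio: 1/(1-f)

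| Assumed f | 1/(1-f) |
| --- | --- |
| 10% | 1/0.90 = 1.11 |
| 25% | 1/0.75 = 1.33 |
| 50% | 1/0.50 = 2.00 |

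*Worked example.* Take the 3,500-employee authority. Assume 60% are emailed (2,100), with 60 completers through the email link and 30 through a poster or the portal. As written: 90/2,100 = 4.29%. Matched to the email route: 60/2,100 = 2.86%. The ratio is 1.5, which agrees with 1/(1-f) at f = 30/90.

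Some emailed staff may come in through the portal. If the rate is meant as uptake by any route among emailed staff, only completers who were not emailed are misplaced. The excess is then smaller than 1/(1-f) gives.

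**Step 3: effect on comparison between sites.** Suppose two sites each email 2,100 staff and each get 60 completers from the email. One uses email alone; the other gets 60 more from posters. They report 60/2,100 = 2.86% and 120/2,100 = 5.71%, although the email response is identical.

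**Step 4: what a common denominator gives.** At the target of 30 completers, the rate on total workforce is 30/700 = 4.29% at the manufacturer, 30/2,700 = 1.11% at the hospital and 30/19,000 = 0.16% at the largest authority. It exists at every site whatever the route.

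**Step 5: how far the headline would move.** If a share e of the workforce is emailed, completers over emailed staff is 1/e times completers over workforce. At the 700-employee site with 30 completers this is 30/630 = 4.76% for e = 0.9 and 30/210 = 14.29% for e = 0.3, or 1.11 and 3.33 times the workforce figure. This step compares two different quantities and does not measure an error.

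**The case against.** The strongest reply is that the paragraph opens by limiting itself to organisations that recruit by email, and that the recruitment sentence, which again refers to email, is meant to sit inside that limit. On that reading an email-only site has two coherent rates. This stands. It does not supply a definition for a site using only posters, portal or newsletter, and it does not restrict the numerator at a site using email alongside other routes.

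A second reply is that the work-email percentage measures how far an email campaign can reach, not who may join, and that the protocol already collects job-type data to show any inequality this creates. That is largely fair. The label and the wording about restricting inclusion conflict with the Participants section, and rewording resolves this.

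A third is that the analysis is largely descriptive, the target of 30 is a count that no denominator affects, and the unseen statistical analysis plan may define further rates. All true. Retention and the AUDIT-C percentage are also unaffected, because both use completers as the denominator. A later plan cannot, however, recover a route of entry that was never recorded.

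A reader might go further in three ways that the protocol does not support:

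- *The eligibility rate is inflated by a work-email denominator.* Work email is its numerator. Measured against the Participants section, it would be too low at email sites.
- *Uptake is overstated by one over email coverage* (1/0.6 = 1.67 in the worked example). That sets response among emailed staff against workforce uptake (90/3,500 = 2.57%). The ratio would arise at a purely email site too, and the protocol does not present its rate as workforce uptake.
- *The proportion drinking above the threshold is missing.* AUDIT-C of five or more among completers is already reported.

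**Conclusion.** The point holds in limited form. Followed as written, the recruitment rate is mismatched at any site that mixes routes and cannot be computed at any site that does not email. At the latter the eligibility rate has no definition either. The overstatement at a mixed site is 1/(1-f) against the route-matched email rate, or 1.11 to 2.00 for f between 10% and 50%. That range is an assumption, since the protocol gives no figure for f.

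It might be inferred that several sites will certainly be affected. The protocol does not support this: it lists permitted routes but not the routes each site chose, so the number could be anything from none to six. The point still deserves correction before recruitment opens. The rule is stated rather than merely left open, it governs a parameter that feeds the feasibility decision, and the missing route information cannot be rebuilt afterwards.

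**What to change.** 1. Report health-screen completers over total workforce for every organisation, using the sizes in the Setting section. This gives one rate that exists and compares across all six.
2. Record the route of entry, by a separate link for each channel or one question on the study website. The question also covers people who type in an address from a poster.
3. Report completers who came through the email link over employees emailed as a separate rate, at sites that email.
4. Relabel the work-email percentage of the workforce as *email reach*, so that it is not taken for eligibility.
5. Reconcile the wording in Outcomes and outcome measures that treats inclusion as restricted to work-email holders with the Participants section, which sets no such condition.

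The cost is a few sentences of protocol text and minor website work. The headline recruitment percentage will look lower wherever fewer than all staff are emailed.
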